***Quality of life and patient satisfaction***
EuroQol 5D survey
State Trait Anxiety Inventory questionnaire
Edinburgh Postnatal Depression Score questionnaire
Investigator-designed remote monitoring feasibility surveys (*interventional arm only*)
Qualitative interview with participants and clinicians *(interventional arm only)*

The satisfaction and quality of life of every participant will be surveyed with the EuroQol-5D-3L [41], State Trait Anxiety Inventory [42] and Edinburgh Postnatal Depression Score questionnaires [43]. Surveys will be sent by email at study baseline, at 28 weeks’ gestation and 6 weeks after delivery. Additionally, participants in the interventional arm will complete investigator-designed surveys to assess the technological feasibility of remote monitoring.

Qualitative interviews will be undertaken after the endpoint of the study using a mixed-methods approach, focusing on the experiences of clinicians and midwives involved in the study, as well as a group of consented participants from the interventional arm. Interviews will be conducted either in person or through virtual video conference, by an investigator not previously known to the participants during their pregnancy. All audio from the interviews will be recorded to allow for transcription, and numbers of participant to be determined by assessment of data saturation.

Australia has a universal healthcare system and as such Medicare is a national system that funds and also collects accurate data regarding episodes of health care delivery in the community including investigations, admissions, primary health review and medication prescription. Therefore, utilisation of healthcare resources will be assessed through collection of data from the Medicare Benefits Schedule (MBS) and Pharmaceutical Benefits Schedule (PBS). The cost-effectiveness of remote blood pressure monitoring will be assessed from the perspective of both patients and the healthcare system based on this data.

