The dichotomous primary outcome will be analysed using a generalised linear model (with binomial distribution and log link), adjusting for minimisation variables, chronic hypertension and aspirin use. Treatment effects will be expressed as adjusted risk ratios with 95% CIs. The secondary outcomes that are binary will be analysed using the same methods described for the primary outcomes, with corresponding 95% CIs. For those secondary outcomes that are continuous, data that is normally distributed will be analysed with parametric tests and non-normally distributed data will be analysed with non-parametric tests. Significance will be set at 0.05 and adjustments for multiple comparisons will be made where comparing several groups.

Subgroup analyses will be undertaken on (i) variables used in the minimisation algorithm (i.e. hypertension type [chronic or gestational hypertension] and LDA use); and (ii) other variables of prognostic significance pre-specified as ethnicity, body mass index, prior severe hypertension in the index pregnancy, antihypertensive therapy at randomisation, gestational diabetes mellitus at randomisation, and smoking status at randomisation. Subgroup analyses will be limited to the primary outcome. Results will be presented as adjusted risk ratios with 95% confidence intervals. The results of subgroup analyses will be treated with caution and will be used for the purposes of hypothesis generation only.

Participants with missing primary outcome data will not be included in the primary analysis in the first instance. This presents a risk of bias, and sensitivity analyses will be undertaken to assess the possible impact of the risk. Sensitivity analyses will also be undertaken for the women who were randomised to the conventional care arm, who had a remote blood pressure monitor at home. A post-hoc analysis will be undertaken for aspirin compliance as a modifier based on PFA-100 levels.

Comparison of questionnaires will be made for each time point.

A’within trial’ economic evaluation will be conducted alongside the trial from a health sector perspective, and extending to patient and carer costs. This will combine three forms of complimentary economic analysis in a comprehensive approach.

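### Secondary outcomes: adjusting the 28-week and 6-week questionnaire scores for the baseline score already collected would gain precision at almost no cost

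*Protocol article*

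**What the plan says.** Under Outcome measures, the article says "The satisfaction and quality of life of every participant will be surveyed with the EuroQol-5D-3L", together with the State Trait Anxiety Inventory (STAI) and the Edinburgh Postnatal Depression Score (EPDS). The timing is "Surveys will be sent by email at study baseline, at 28 weeks’ gestation and 6 weeks after delivery". Each instrument therefore yields one baseline and two follow-up scores in both arms.

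Under Data handling, analysis and result reporting:

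- Primary outcome: a binomial model with log link, "adjusting for minimisation variables, chronic hypertension and aspirin use", giving adjusted risk ratios with 95% confidence intervals.
- Binary secondary outcomes: "The secondary outcomes that are binary will be analysed using the same methods described for the primary outcomes, with corresponding 95% CIs".
- Continuous secondary outcomes: "data that is normally distributed will be analysed with parametric tests and non-normally distributed data will be analysed with non-parametric tests".
- Questionnaires: "Comparison of questionnaires will be made for each time point".
- Significance level: "Significance will be set at 0.05 and adjustments for multiple comparisons will be made where comparing several groups".

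Study population names three minimisation factors: chronic hypertension, centre and aspirin use.

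**The concern.** For binary outcomes the plan names a model, covariates, an effect measure and an interval. For continuous outcomes it names a class of test and how to choose within it. For the questionnaires it adds only that comparisons are made time point by time point. Nothing says that the baseline score enters the follow-up comparison, or that the minimisation factors do.

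A woman's anxiety, mood or quality-of-life score before the intervention usually predicts her later score. A comparison that ignores it carries between-woman variation that could have been removed. A rank test, where chosen, also gives no mean difference on the scale of the instrument. Patient satisfaction is among the stated aims, and these are the validated patient-reported scales compared between both arms. At stake is how precisely the trial can report on them, with numbers set for a different outcome.

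**Working it through.** **Inputs from the article.** 1:1 allocation. Sample size section: event rate 31.1%, non-inferiority margin 15 percentage points, one-sided alpha 0.05, power 0.80, 118 per arm, 130 recruited per arm with 20% attrition. Significance for secondary outcomes 0.05, taken as two-sided to match the 95% intervals.

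**Assumptions.** The article gives no baseline-to-follow-up correlation r, so r = 0.5 is assumed, with a range of 0.3 to 0.7. It gives no questionnaire sample size or response rate, so 118 per arm is borrowed from the primary outcome and means full response.

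**Step 1. Reproduce the stated size.** n = (z₀.₉₅ + z₀.₈₀)² × 2p(1 − p) / margin² = (1.645 + 0.842)² × 2 × 0.311 × 0.689 / 0.15² ≈ 117.8, which rounds up to 118 per arm. This matches the article.

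**Step 2. Detectable difference without baseline.** In SD units, with 80% power: (z₀.₉₇₅ + z₀.₈₀) × √(2/n) = (1.960 + 0.842) × √(2/118) = 0.365 SD.

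**Step 3. With baseline as covariate.** The residual variance is multiplied by 1 − r², so the detectable difference is multiplied by √(1 − r²). The last two columns give the unadjusted sample size with equal precision, 118/(1 − r²), and the power for an illustrative true difference of 0.3 SD.

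| r (assumed) | Variance cut | Detectable difference (SD) | Equivalent n per arm | Power at 0.3 SD |
|---|---|---|---|---|
| no baseline used | none | 0.365 | 118 | 63.5% |
| 0.3 | 9% | 0.348 | 130 | 67.6% |
| 0.5 | 25% | 0.316 | 157 | 75.8% |
| 0.7 | 51% | 0.260 | 231 | 89.7% |

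**Step 4. Lower response.** If 20% of the 130 per arm are lost, 130 × 0.8 = 104 remain. The detectable difference is then 0.389 SD without baseline and 0.336 SD at r = 0.5 (0.371 at r = 0.3, 0.277 at r = 0.7). The proportional gain is the same.

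**Step 5. Baseline as a time point.** If arms were significance-tested on scores completed before allocation, the null would be true by design. Three independent tests at 0.05 would give at least one false signal with probability 1 − 0.95³ = 14%.

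**Step 6. Scope.** Steps 2 to 4 apply only to outcomes with a baseline value. Birthweight and gestational age at delivery, both in Table 3, have none. For these only adjustment for the minimisation factors is available, and no gain has been calculated for it.

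**The case against.** The article never calls these tests unadjusted. That reading rests on contrast with the neighbouring sentences. ANCOVA is a parametric method, and a fuller analysis plan that is not shown may already specify it. This stands, and for that reason the point is an improvement to the stated method and not an error. What remains is that the article does state a method for continuous outcomes, and a better one is available from data already being collected.

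The size depends wholly on an assumed correlation, and the range is wide. This also stands. Even so, the direction is the same for any appreciable correlation.

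Three stronger readings are tempting, and the article does not support them.

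- A reader might infer that a significance test at baseline is planned, because baseline is one of the three time points. The text says comparison, not test, and a descriptive comparison at baseline is ordinary reporting. The 14% in the working applies only if tests were done.
- A reader might infer that the follow-up comparisons would be biased or unreliable. In a randomised trial they are valid without baseline adjustment, because chance imbalance is already reflected in the standard error. The loss is one of efficiency.
- A reader might infer that rank tests would leave the cost-utility analysis without an effect estimate. The economic section derives QALYs from EQ-5D and forms net benefit separately, without using these tests.

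A further caution concerns the remedy. The baseline survey is emailed, and the article does not say that it is completed before allocation. In an unblinded trial, a score given after allocation may already reflect knowledge of the arm.

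**Conclusion.** This is a free improvement to secondary outcomes. The article plans time-point comparisons of EQ-5D-3L, STAI and EPDS without stating any use of the baseline score, and gives continuous outcomes neither the adjustment nor the effect estimates that it gives binary ones. With r assumed at 0.5, using baseline would give the precision of about 157 women per arm from 118 (130 to 231 over the range 0.3 to 0.7). That rests on the assumed correlation, on full questionnaire response and on a baseline score from before allocation. The non-inferiority conclusion does not depend on it.

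**What to change.** - **EQ-5D-3L, STAI and EPDS.** Analyse the 28-week and 6-week scores by ANCOVA, or by a repeated-measures mixed model covering both times, adjusted for the baseline score and for chronic hypertension, centre and aspirin use. Report adjusted mean differences with 95% confidence intervals, robust or bootstrap if the scores are skewed. This replaces choosing a test by normality.
- **Baseline scores.** Present them descriptively by arm, without a significance test. Use as the covariate a survey completed before allocation, and say so in the plan.
- **Continuous outcomes without a baseline value,** such as birthweight and gestational age at delivery. Adjust for the minimisation factors only, in line with the binary outcomes, and report adjusted mean differences with 95% confidence intervals.

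The cost is a few sentences in the analysis plan and slightly more analysis work. If the baseline survey does not already precede allocation, its timing must also be changed. No extra data or recruitment is needed.

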### Sample size

The sample size calculation is based on the assumption that the composite foetal outcome will be equal in the remote BP monitoring and control groups: a non-inferiority trial. Prior data indicates that the rate of the composite foetal outcome is approximately 31.1%, drawn from a study previously undertaken in the local high-risk pregnant population [4]. Investigators made a reasoned choice about the acceptable difference in adverse foetal outcome and feasibility of the trial. As a result, the non-inferiority margin was defined as a 15% absolute increase or less in the remote BP monitoring group. With a one-sided α of 0.05, the study will achieve a power of 0.80 if 118 women will be included in each trial arm. Furthermore allowing for a 20% attrition rate, 260 participants will be needed in total, 130 participants in each arm.

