First, a cost effectiveness analysis (CEA) will compare remote monitoring against usual care and estimate the incremental cost per change in the primary composite adverse patient outcome. In the non-inferiority approach, it is hypothesized that remote monitoring will reduce costs with no significant change in outcomes. Costing will consider the difference in implementing the model of care between trial arms. In usual care, this will include the time cost of each specialist visit, and the time and travel cost of patients (and carers, if relevant). In remote monitoring, this will include the cost of each unit of equipment, development of training, and time in undertaking educational training (professional and patient), specialist time to review BP readings, and patient visit to specialists (similar to usual care, describe above). MBS will be used to cost professional time and average hourly wage rates used to value for patient/carer time. For both trial arms, health care utilisation will be compared and costed using reference costs from the Independent Hospital Pricing Authority (IHPA).

Secondly, a cost-utility analysis (CUA) will compare trial arms and estimate the incremental cost per change in ‘health utility’ as the outcome measure, replacing the composite adverse outcome. Health utility is an indexed measure of (preference-weighted) patient quality of life, will be measured by the EQ5D and used to generate quality-adjusted life years (QALYs). QALYs will then be converted to dollar values by multiplying each QALY by $50,000. By combining monetized QALYs and costs a measure of ‘net benefit’ is generated where a positive value indicates value for money.

Thirdly, a value of information (VOI) analysis will then estimate statistical uncertainty whether remote monitoring is cost-effective. In a Bayesian analysis, an estimate of the economic value of undertaking further research will be made to reduce parameter uncertainty (cost and outcomes) and increase confidence that remote monitoring is cost-effective. The VOI will then extend to investigate subgroup heterogeneity and to explore whether remote monitoring is relatively more (or less) cost-effective in particular groups, to inform whether further research can best focus on subgroups where uncertainty is greatest.

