## Discussion

The REMOTE CONTROL trial will be the first non-inferiority randomised controlled trial, powered to evaluate maternal and foetal outcomes conducted within the Australian healthcare system. A composite foetal events outcome was chosen as the primary outcome, as this represents a definitive end-point relevant to clinicians, patients and the healthcare system. If foetal and secondary outcomes from this study are similar with the institution of remote monitoring, there are major potential benefits to patients and the healthcare system. Through reducing the travel costs, clinic visits and waiting times, it is likely to lead to improved compliance for all patients. In addition, it could improve delivery of care to vulnerable populations in rural and remote communities in Australia, which has unique geographic and social considerations.

The trial is designed to be a pragmatic non-inferiority randomised controlled trial. The underlying pathophysiology of HDP is not going to be altered by the proposed intervention, and therefore a non-inferiority trial design was opted for.

The participant population will be those deemed to be high risk for developing a hypertensive disorder of pregnancy. It is this group of women who are currently being referred to and monitored in an Obstetric Medicine clinic within our local health district. This leads to additional visits throughout their pregnancy, in addition to routine antenatal care. In this high-risk population, the rate of HDP in a recent study set in South Western Sydney was 33.8%, with the rate of adverse foetal outcomes (intrauterine growth restriction or pre-term delivery) between approximately 15–17% (4). Therefore, the high incidence of HDP and foetal adverse outcomes in this population lends itself to an adequately powered study without requiring overwhelming numbers to detect a difference between the groups.

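### The economic hypothesis describes non-inferiority as the absence of a significant change, not as meeting the 15-point margin, and the planned cost-effectiveness ratio divides by a difference that the design assumes to be zero

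*Protocol article*

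**What the plan says.** Protocol article, Sample size: "the non-inferiority margin was defined as a 15% absolute increase or less in the remote BP monitoring group". The calculation assumes that "the composite foetal outcome will be equal in the remote BP monitoring and control groups", with a control rate of about 31.1%, a one-sided α of 0.05, power 0.80 and 118 women per arm.

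Protocol article, Data handling, analysis and result reporting: the primary outcome is to be summarised by adjusted risk ratios with 95% confidence intervals, and the general significance level is 0.05. The section commits to the CONSORT extension for non-inferiority trials but does not restate the margin. In its economic part it says, of the non-inferiority approach, that "it is hypothesized that remote monitoring will reduce costs with no significant change in outcomes".

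Three economic analyses follow:
- a cost-effectiveness analysis, which will "estimate the incremental cost per change in the primary composite adverse patient outcome";
- a cost-utility analysis on EQ-5D quality-adjusted life years, which take the place of the composite, and in which "a measure of ‘net benefit’ is generated where a positive value indicates value for money";
- a Bayesian stage, in which "a value of information (VOI) analysis will then estimate statistical uncertainty whether remote monitoring is cost-effective".

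**The concern.** Failing to find a significant difference is not the same as excluding an increase of 15 points or more. The first is easier to achieve the less information a trial holds; the second is harder. The economic sentence carries the non-inferiority label but describes the first. A report of lower cost with no significant change would fit the stated hypothesis even when the trial had missed its own margin.

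The planned summary offers little protection. Of the three economic analyses, only the cost-effectiveness ratio is expressly built on the foetal composite, and its denominator is a difference that the sample size section sets to zero. The net benefit that could stand in for the ratio is planned on maternal health utility alone.

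**Working it through.** **Inputs.** From Sample size: control rate 0.311, equal rates assumed, margin 0.15, one-sided α 0.05, power 0.80, n = 118 per arm. From the analysis section: significance level 0.05, taken here as two-sided because 95% intervals are reported. That is an assumption, since the sidedness is not stated.

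**1. The plan's own figure.**
n = (1.645 + 0.842)² × 2 × 0.311 × 0.689 / 0.15² = 117.8, so 118 per arm. It reproduces.

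**2. Where the two criteria part, with truly equal outcomes.**
- SE of the risk difference = √(2 × 0.311 × 0.689 / 118) = 0.0603.
- Non-significant: observed difference within ±1.96 × 0.0603 = ±0.118.
- Margin met: observed difference below 0.15 − 1.645 × 0.0603 = 0.051.
- An observed excess of about 5.1 to 11.8 points is therefore non-significant and also fails the margin.
- Its probability is Φ(0.118/0.0603) − Φ(0.051/0.0603) = 0.975 − 0.801 = 0.174, or about 17%.

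Non-inferiority fails in about 20% of such trials by design. These 17 points are most of that.

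**3. At a true increase equal to the margin (31.1% against 46.1%).**
- SE = √[(0.311 × 0.689 + 0.461 × 0.539)/118] = 0.0626.
- Non-significant: Φ(1.96 − 0.15/0.0626) = Φ(−0.435) = 0.33. A pooled-variance test gives 0.34.
- Non-inferiority declared: Φ(0 − 1.645) = 0.05.
- Non-significant and failing the margin: 0.28 by simulation.

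With 104 to 130 evaluable women per arm, the simulated non-significant share runs from 39% to 30%. The non-inferiority share stays at about 5%.

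**4. The ratio.** Define it literally as cost difference divided by change in the adverse composite (remote minus usual care).

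| | Fewer adverse outcomes | More adverse outcomes |
|---|---|---|
| Lower cost | positive | negative |
| Higher cost | negative | positive |

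A positive value covers both the best result and the worst one. A negative value covers both trade-offs.

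With equal true rates the outcome difference is symmetric about zero. The two arms have identical counts with probability about 1/[√(2π) × √(118 × 2 × 0.311 × 0.689)] = 0.399/7.11 = 0.056, and the ratio is then undefined. If cost and outcome differences are independent, the ratio is positive with probability (1 − 0.056)/2 = 0.47, whatever the size of the saving.

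The spread in dollars cannot be fixed from the documents, which give no cost figures. For assumed savings of $250 to $1,000 per woman and assumed cost SDs of $1,000 to $10,000, the central 95% of the ratio runs from about ±$33,000 to about ±$180,000 per adverse outcome.

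**The case against.** The strongest reply is that the sentence is a hypothesis. Nowhere does the article say that p > 0.05 counts as equal outcomes, or that a cost-saving claim follows from it. The phrase sits under a non-inferiority label and can be read as shorthand for the margin. The CONSORT non-inferiority extension is promised, the primary outcome will appear with its interval, and the economic analyses estimate quantities instead of testing them. All of this stands, and it limits the point. A reader might infer that the plan lets a non-significant test trigger the economic conclusion; the document contains no such rule.

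A reader might also be drawn to a smaller harm. A true 10-point increase would be non-significant in about 64% of trials at 118 per arm. The arithmetic is right, but the 10 points appear nowhere in the documents and lie inside the margin that the protocol accepts, so missing such an increase does not contradict its standard. The fair comparisons are at the margin and at equality.

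Nor does the article's Discussion, with "If foetal and secondary outcomes from this study are similar with the institution of remote monitoring, there are major potential benefits", add a second criterion. It is narrative and sets no analysis.

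Finally, net benefit and joint uncertainty are already planned, and a condensed article may leave their detail to a full economic plan. That is true of detail. But the article does state that health utility replaces the composite in the net benefit, and it does choose a ratio for the composite.

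**Conclusion.** The point holds as an inconsistency of wording plus a poor choice of summary. The economic hypothesis is looser than the margin, and nothing in the analysis section brings it back to the margin. At a true increase equal to the margin, about 33% of trials would fit the wording on outcomes while 5% would be declared non-inferior. At true equality about 17% would fit it and still fail the margin; no excess harm exists in that case, and the figure is mostly the designed type II error.

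These figures rest on 118 evaluable women per arm, 31.1% in control, unadjusted normal-approximation intervals and a two-sided 0.05 test.

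The ambiguity of the ratio's sign is arithmetic. The 47% needs only equal true rates and independence of cost and outcome differences. No dollar range should be quoted as a property of this trial. The primary non-inferiority conclusion is not affected by this point.

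**What to change.** In the economic part of the analysis section, replace the phrase about no significant change with a statement that the primary foetal outcome is non-inferior within the margin of the Sample size section. State that cost saving at maintained outcome will be claimed only if the upper confidence limit for the risk difference lies below that margin, at the confidence level used for the primary non-inferiority conclusion. Otherwise, report the cost and outcome differences without that claim. This needs a risk-difference estimate beside the planned adjusted risk ratio.

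For the cost-effectiveness analysis, replace the lone ratio with the joint cost and outcome differences and their uncertainty on the cost-effectiveness plane. Add net benefit over a range of values per adverse foetal outcome avoided.

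No new data or participants are needed. The cost is a modest amount of extra analysis, and the claim of savings at maintained outcome is lost whenever the margin is missed, even if p > 0.05.

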Participants will be asked to take 3 readings, 5 min apart while sitting quietly at any time of the day. The first reading will be disregarded, and the higher of the last two readings will be recorded. This will occur on 3 occasions every week. The blood pressure reading, in addition to a symptom check-list through the M♡THer application, will be uploaded to a secure web-based dashboard. A pre-specified evidence-based algorithm built-in to the M♡THer application (Table 2), consistent with NICE guidelines for BP targets in pregnancy [2], will provide instructions to the patient. Patient data uploaded to the dashboard will be reviewed three times a week by an obstetric medicine clinician. Possible steps in the management, after the uploaded results are checked are (1) expectant management, (2) titration of medications by telephone call, (3) participant booked to attend a Telehealth appointment with the Obstetric Medicine clinic, (4) same-day clinical assessment or (5) hospital admission. Should hospital admission be necessary due to clinical deterioration, the patient will be monitored in the hospital as per local protocol and all relevant data will be collected. If discharged, women will continue remote BP monitoring until 6 weeks postpartum. All events of healthcare utilisation including imaging, pathology tests, consultations in the outpatient department and community-based care as well as ward admissions will be recorded.

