***Feasibility and acceptability***
Compliance with remote monitoring *(interventional arm only)*
Compliance with face to face consultations
Number of phone calls from the investigator *(interventional arm only)*
Recruitment rate
Persistence with remote monitoring

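### The remote-arm cost list omits women's recurring self-measurement time, so the patient-inclusive cost comparison, costed as listed, leans toward remote monitoring

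*Protocol article*

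**What the plan says.** The section on data handling, analysis and result reporting describes a within-trial economic evaluation "from a health sector perspective, and extending to patient and carer costs". The outcome section likewise says cost-effectiveness will be judged for both patients and the healthcare system. The same analysis section gives the expected result: "it is hypothesized that remote monitoring will reduce costs with no significant change in outcomes".

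Cost items are then listed by arm.

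- Usual care: "In usual care, this will include the time cost of each specialist visit, and the time and travel cost of patients", with carers added where relevant.
- Remote arm: "In remote monitoring, this will include the cost of each unit of equipment, development of training, and time in undertaking educational training", the training time being that of both staff and women. The list continues with specialist time to review readings, and specialist visits costed as in usual care.

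Professional time is costed from the MBS, and patient and carer time at average hourly wages. Healthcare utilisation in both arms is costed from IHPA reference costs.

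The intervention section sets the home-measurement schedule: "Participants will be asked to take 3 readings, 5 min apart while sitting quietly at any time of the day" and "This will occur on 3 occasions every week". A symptom checklist is uploaded as well.

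**The concern.** Home measurement is the main continuing task that the intervention gives to women. An evaluation that counts patient time should count it, as it counts the time spent on the clinic visits that remote monitoring is meant to reduce. The remote-arm list is detailed enough to name one-off training time, yet it stops short of the recurring time.

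Scheduled self-measurement falls only on the remote arm. Leaving it out therefore lowers that arm's patient cost, which is the direction of the hypothesised saving. The effect passes into the patient-inclusive incremental cost, into the net benefit (which combines monetised QALYs with costs), and into any value-of-information analysis built on those costs. Cost-effectiveness is a stated aim of the trial, so the comparison should rest on the same kinds of patient time in both arms.

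**Working it through.** The plan gives no figure to reproduce here. The check compares the two lists and then counts the unlisted time.

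**Patient time in the two lists**

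| Patient-time item | Usual care | Remote arm |
|---|---|---|
| Time and travel for specialist visits | listed | listed (as in usual care) |
| Training time | not applicable | listed |
| Scheduled home readings | not applicable | not listed |

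**Inputs from the protocol article**

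- Three readings 5 minutes apart contain two gaps, so a session lasts at least 2 × 5 = 10 minutes.
- There are 3 sessions a week, so at least 3 × 10 = 30 minutes a week.
- Enrolment is before 28 weeks (Table 1).
- Monitoring to 6 weeks postpartum is stated in the intervention section for women discharged after an admission.
- Usual care brings 6–8 additional clinic reviews (design and setting).

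**Assumptions**

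- Enrolment at 12, 20 or 27 weeks.
- Birth at 38 or 39 weeks.
- The 6-week postpartum period applies to all remote-arm women.
- Full adherence.

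**Formula**

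Hours = 3 × (birth week − enrolment week + 6) × minutes per session ÷ 60.

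| Enrolment | Birth | Weeks | Sessions | Hours at 10 min |
|---|---|---|---|---|
| 12 | 39 | 33 | 99 | 16.5 |
| 12 | 38 | 32 | 96 | 16.0 |
| 20 | 39 | 25 | 75 | 12.5 |
| 20 | 38 | 24 | 72 | 12.0 |
| 27 | 39 | 18 | 54 | 9.0 |
| 27 | 38 | 17 | 51 | 8.5 |

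The range is 8.5 to 16.5 hours per woman.

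**Sensitivity to the assumptions**

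- At an assumed 15 minutes a session (cuff, rest, checklist): 8.5 × 1.5 = 12.75 to 16.5 × 1.5 = 24.75 hours.
- At an assumed 70% adherence and 10 minutes: 8.5 × 0.7 = 5.95 to 16.5 × 0.7 = 11.55 hours.
- If monitoring stopped at birth, 6 × 0.5 = 3 hours come off: 5.5 to 13.5 hours.

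**What would be needed to set this against the time saved**

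If all 6–8 extra reviews were avoided, the unlisted time would equal 8.5 ÷ 8 ≈ 1.1 to 16.5 ÷ 6 = 2.75 hours per avoided visit. The documents state neither the length of a visit with travel nor the number of visits avoided, so the comparison stops there.

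**The case against.** The strongest reply is that nothing is expressly excluded. Both lists are introduced as what costing will include. The perspective covers patient costs in general, and the wage-rate rule is not limited to one arm. A fuller health-economic plan might add the item. This lowers the certainty that the time will go uncosted, but it does not remove the point. The article publishes arm-specific lists beside a patient-and-carer perspective, and the lists as written do not match that perspective on the largest scheduled patient task.

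Two further replies stand in part. Control women may measure at home too, and that time is not named either; but it is unscheduled and not encouraged, so it is likely to be smaller. Valuing 10 minutes of sitting quietly, at a time the woman chooses, at a full wage is open to dispute. That is a reason to show the result both ways, not to leave the item out.

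A reader might infer three stronger things, which the documents do not support.

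- *That staff telephone contacts and Telehealth go uncosted.* Titration calls follow the review of readings and may fall under the costed review time. Telehealth appointments may count as specialist visits. Contacts with the health system are recorded, and utilisation is costed in both arms. Calls are counted in Table 3 ("Number of phone calls from the investigator"); their place under feasibility does not show that they are left out of the costs.
- *That patient time is always costed in favour of remote monitoring.* The remote arm is charged for women's training time and for their time and travel at visits.
- *That the omitted time is about as large as the time saved.* Visit duration, adherence and visits avoided are not given. Travel, carer and specialist costs also form part of any saving, so equal hours would not cancel it.

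**Conclusion.** The point holds for self-measurement time. Under the declared patient-and-carer perspective, costing the arms as listed charges usual care for visit time and travel but does not charge the remote arm for the recurring readings. The patient-inclusive incremental cost and net benefit then lean toward remote monitoring. The health-sector result does not change with this item, and neither the primary outcome nor trial conduct is touched.

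The direction follows from the text; the size does not. The minimum of 30 minutes a week is fixed by the schedule. The 8.5 to 16.5 hours per woman rests on the assumed enrolment and birth weeks, on full adherence, and on monitoring to 6 weeks postpartum for every woman. The amount in money, and the share of the hypothesised saving at stake, cannot be derived from the documents. The change is worth making before the economic analysis, because it is cheap and concerns a stated aim.

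**What to change.** In the economic evaluation part of the data handling, analysis and result reporting section:

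1. Add women's self-measurement time to the remote-arm patient costs: uploaded sessions × a stated number of minutes per session × the average hourly wage rate already chosen for patient and carer time.
2. Report the patient-inclusive incremental cost and net benefit with and without this item, beside the health-sector result.
3. As a clarification only, state that staff time on telephone titration calls is included in the costed professional time.

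The app already uploads the sessions, calls are already counted and the wage rate is already set. The cost is a few sentences, a justified minutes-per-session figure and a little more costing work. The reported saving may turn out less favourable. Recruitment, sample size and trial procedures do not change.
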